## 2.6 Sample Size

A sample size of 1414 women with GDM will provide 90% power ( $2\alpha=0.05$ ) to detect a relative risk of 0.65, assuming that the control group cumulative incidence for change in glycaemic category will be 20% at 24 months and allowing for 20% of missing outcome data.

The initial power calculation was based on a chi-square test comparing two proportions at 24 months; however, to account for various study durations, the primary analysis will consist in a survival analysis of time to change in glycaemic category which is expected to have at least the same power as a comparison of proportions.

### 3 Data handling and reporting rules

---

#### 3.2 Analysis Sets

All analyses will be based on the principle of intention-to-treat, i.e. by analysing subjects according to the group they were randomised to and regardless of compliance. The ITT will include all enrolled subjects who are randomised and have a baseline with respect to the efficacy evaluation of this study. Mis-randomised subjects will not be part of the ITT analysis.

Analyses of the primary and secondary outcomes will be repeated after including the 11 mis-randomised subjects. This will be indicated in the relevant sections of this SAP.

#### 3.3 Baseline values

The last data available recorded at or prior to the randomisation visit will be used as baseline values unless otherwise specified.

#### 3.4 Handling of last (EOS) visit

Given study participants entered the study at different times and were followed for various durations, the End of Study (EOS) visit will occur at different times for different participants.

For longitudinal analyses and descriptive analyses by visit, EOS visits will be re-allocated according to the planned visit schedule (i.e. Month 1, 6, 12, 18, 24 or 30). The allocation, based on the number of days between the date of randomisation and the EOS visit, will be done as follows:

- Month 6: number of days between 93 and 273 (inclusive)
- Month 12: number of days between 274 and 456 (inclusive)
- Month 18: number of days between 457 and 638 (inclusive)
- Month 24: number of days between 639 and 821 (inclusive)
- Month 30: number of days between 822 and 1003 (inclusive)
- Month 36: number of days between 1004 and 1186 (inclusive)

#### 3.5 Early study discontinuation/Lost to Follow-up

Early termination is captured on the CRF and may be due to one of the following reasons:

- Withdrawal of Informed consent for follow-up visits
- Development of T2DM
- Occurrence of pregnancy
- Unable to contact or unable to follow-up

In case of early termination, a patient was expected to have an EOS visit completed at the time of termination. For those who did not terminate early, EOS visits with at least partial data collection were to be conducted after 1 July 2020.

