### **3.6 STATISTICAL METHODS**

Analysis will be based on the principle of intention-to-treat. The effectiveness of the study intervention on the primary outcomes will be determined using Cox models for survival data, with censoring of participants who develop a subsequent pregnancy during follow-up. Given that the occurrence of primary outcomes can only be registered to the date of ascertainment during study visits, the use of other methods (e.g. Poisson regression) for the primary analysis will be explored during the blind review and will be finalised in the Statistical Analysis Plan prior to database lock and unblinding. Analyses of secondary outcomes will be conducted using standard statistical procedures applicable to dichotomous, categorical or continuous data as appropriate.

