#### **5.1.5 EOS visit (End of study)**

1. Measure weight, waist circumference, and blood pressure.
2. Determine whether an interim diagnosis of T2DM has been made.
3. If an interim diagnosis of T2DM has been made, obtain confirmatory source documentation.
4. If an interim diagnosis of T2DM has not been made, perform OGTT and measure HbA1c.
5. Administer diet and physical activity questionnaires.
6. Record healthcare utilisation since the last study visit.
7. Record any serious adverse events since the last study visit.

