### 4.1 General Principles

Analyses will be performed using SAS Enterprise Guide version 8.3 or higher (SAS Institute Inc., Cary, NC, USA).

All variables will be analysed by descriptive statistical methods. The number of data available and missing data, mean, standard deviation, minimum, quartiles, median, and maximum will be calculated for continuous data. Frequency tables will be generated for categorical data. For categorical variables, the number and percentage of patients with a specific level of the variable will be presented.

All tests will be two-sided with a type-I error rate of 5%. Analyses of the primary outcome (change in category of glycaemia from normoglycaemia to IGT, IFG or T2DM or from IFG or IGT to T2DM) will be unadjusted for multiplicity; however, we will control the family-wise error rate across secondary outcomes using a Holm-Bonferroni correction [2]. No other multiplicity adjustment will be applied.

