### 4.9.2 Survival analysis

Change in glycaemic category for primary outcome as defined in section 2.4.1 will be analysed as a time to event calculated as the number of days between randomisation and the day of the event. For subjects with no event, data will be censored on the day of the last OGTT test results.

Survival by treatment arm will be described using a Kaplan-Meier plot with 95% confidence interval will be reported by treatment arm. If available, median time to event as well as quartiles will be derived from the Kaplan-Meier estimates. Censoring will be done at time of last OGTT test.

A Cox model will be used to estimate the Hazard ratio of the two arms (Intervention compared to Control). The Cox model will include the randomised group as well as prior use of insulin as fixed effects and study site as a random effect [4]. We will visually assess the proportional hazard assumption. SAS Proc PHREG will be used.

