### 6.1 Tables

*Table 1. Screen failures by reason*

|          | Total (N count) |
|----------|-----------------|
| Reason 1 |                 |
| Reason 2 |                 |
| Etc.     |                 |
|          |                 |
|          |                 |
|          |                 |
|          |                 |

*Table 2. Overall participant disposition*

|                                   | All Subjects | Intervention | Control   |
|-----------------------------------|--------------|--------------|-----------|
|                                   |              |              |           |
| Screened                   | xx           | xx           | xx        |
| Registered                 | xx           | xx           | xx        |
| Randomised                 | xx           | xx           | xx        |
| Randomised and eligible    | xx (xx.x)    | xx (xx.x)    | xx (xx.x) |
| EOS completed              | xx (xx.x)    | xx (xx.x)    | xx (xx.x) |
| Stopped the study early    | xx (xx.x)    | xx (xx.x)    | xx (xx.x) |
| Due to pregnancy           | xx (xx.x)    | xx (xx.x)    | xx (xx.x) |
| Due to development of T2DM | xx (xx.x)    | xx (xx.x)    | xx (xx.x) |
| Lost to follow-up          | xx (xx.x)    | xx (xx.x)    | xx (xx.x) |

Note: Percentages are calculated based on the number of participants randomised. The category 'EOS completed' can include participants who stopped early due to pregnancy and development of T2DM.

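### The SAP does not carry over the protocol's censoring at a subsequent pregnancy, so an OGTT taken in pregnancy can define a primary event or set the censoring date

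*Combined protocol and SAP*

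**What the plan says.** **Protocol.** Section 3.6 sets the primary analysis as Cox models "with censoring of participants who develop a subsequent pregnancy during follow-up". It gives no date for that censoring (conception, detection, or last test before either). It leaves the choice of model open, with Poisson regression as an example, but does not reopen the pregnancy rule. Section 5.1.5 lists the EOS measurements: weight, waist and blood pressure for everyone, and for glycaemia "If an interim diagnosis of T2DM has not been made, perform OGTT and measure HbA1c". Pregnancy is not an exception.

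**SAP.** Section 3.5 names pregnancy among the reasons for early termination and continues: "In case of early termination, a patient was expected to have an EOS visit completed at the time of termination". The note to Table 2 is consistent with this: "The category 'EOS completed' can include participants who stopped early due to pregnancy and development of T2DM". For the primary analysis, SAP 4.9.2 states: "For subjects with no event, data will be censored on the day of the last OGTT test results". SAP 4.9.3 takes its exposure time from the same definition, and 4.9.6 censors at the last relevant glycaemic measure. SAP 3.4 re-allocates EOS visits to scheduled visits for the longitudinal analyses, and 4.10.3 admits every woman with at least one post-baseline value.

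The SAP refers to the index pregnancy as a covariate and subgroup, and tabulates pregnancy as a reason for discontinuation. It states no rule for results obtained during a subsequent pregnancy.

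**The concern.** The SAP's censoring rule is complete enough to program, and it differs from the protocol's. A programmer who follows it would take an abnormal OGTT at a pregnancy-termination visit as a primary event and a normal one as the censoring date. Double programming from the same text would not catch this.

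The trial's own design treats glycaemia in pregnancy as a different quantity. GDM is diagnosed by IADPSG criteria (Protocol 3.2), entry status is established 3 to 18 months post-partum, and outcomes use the ADA cut-offs in SAP 4.9. Every participant has had GDM, so an abnormal OGTT in a new pregnancy may be recurrent GDM rather than the worsening that the trial is about. If such events arise at similar rates in both arms, they pull the estimated effect towards no difference. Pregnancy also occurs after randomisation, so an imbalance between arms would bias the comparison.

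The continuous outcomes are a second, separate gap. Body weight, which the synopsis calls a key secondary outcome, is directly affected by pregnancy, as are waist and possibly blood pressure and fasting glucose.

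**Working it through.** **1. How a result reaches the analysis**

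| Step | Source | Effect |
|---|---|---|
| Pregnancy ends follow-up | SAP 3.5 | Later visits drop out |
| EOS visit expected at that time | SAP 3.5, Table 2 note | The visit falls in pregnancy |
| OGTT, HbA1c, weight, waist, BP at EOS | Protocol 5.1.5 | No exception for pregnancy |
| Any category change is an event; otherwise censor at last OGTT | SAP 4.9.2, 4.9.3 | The OGTT counts |
| EOS data re-allocated; one post-baseline value suffices | SAP 3.4, 4.10.3 | Weight, waist, BP and FBG count |

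The gap is therefore the termination visit itself and any scheduled visit between conception and termination.

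**2. The plan's own figure**

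Inputs from SAP 2.2, 2.6 and 4.1: control risk 0.20, relative risk 0.65 (intervention risk 0.13), two-sided 5% test, 90% power, 20% missing outcomes, 1:1 allocation, chi-square test.

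n per arm = [1.96 × √(2 × 0.165 × 0.835) + 1.2816 × √(0.20 × 0.80 + 0.13 × 0.87)]² / 0.07² = 588.8, rounded up to 589.

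589 × 1.2 = 706.8, rounded up to 707, and 2 × 707 = **1414**. The stated figure is reproduced.

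With 20% missing, 1414 × 0.8 / 2 = 565.6 per arm remain. Power = Φ{[|p₁ − p₂|√n − 1.96√(2p̄(1 − p̄))] / √(p₁(1 − p₁) + p₂(1 − p₂))} = **88.8%**.

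**3. Illustration of size**

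The documents give no pregnancy rate and no crossing rate, so both are assumed: a share c conceives, all of them have an OGTT in pregnancy, and a share q of those tests crosses a category threshold, equally in both arms. With a = c × q, the observed risks are 0.20 + 0.80a (control) and 0.13 + 0.87a (intervention).

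| c | q | a | Control | Intervention | RR | Power as written | Power if all c are lost to censoring |
|---|---|---|---|---|---|---|---|
| 5% | 20% | 1% | 0.2080 | 0.1387 | 0.67 | 86.9% | 87.2% |
| 5% | 40% | 2% | 0.2160 | 0.1474 | 0.68 | 85.0% | 87.2% |
| 15% | 20% | 3% | 0.2240 | 0.1561 | 0.70 | 83.0% | 83.4% |
| 15% | 40% | 6% | 0.2480 | 0.1822 | 0.73 | 76.9% | 83.4% |

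The last column applies the same power formula to risks of 0.20 and 0.13, with 565.6 × 0.95 = 537.3 or 565.6 × 0.85 = 480.8 per arm. It is the worst case for censoring, because women censored at an earlier OGTT still contribute follow-up.

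**4. If pregnancy differed by arm**

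Assume no true effect, pregnancy in 10% of one arm and 5% of the other, and half of the in-pregnancy tests classed as worsened. The arm risks are 0.20 × 0.90 + 0.10 × 0.5 = 0.230 and 0.20 × 0.95 + 0.05 × 0.5 = 0.215. The relative risk is 0.93 or 1.07, depending on which arm has more pregnancies, instead of 1.

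For weight, a 5-point imbalance with an assumed gain of 2-10 kg shifts the mean difference by 0.05 × 2 = 0.1 kg to 0.05 × 10 = 0.5 kg, against the design difference of 1.80 kg in the synopsis. With equal shares and equal gains the shift cancels.

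**The case against.** The strongest reply is that the SAP is based on the protocol, makes pregnancy a reason to stop, and so ends follow-up there; silence on censoring need not mean the rule was abandoned. Part of this stands. Later visits do drop out, and a reader might infer that the SAP deliberately reversed the protocol, which the documents do not show. But SAP 4.9.2 supplies its own censoring date, and that date is not limited to tests before pregnancy. The mismatch remains.

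A reader might also infer that in-pregnancy tests did enter the data. The documents do not establish this. SAP 3.5 says the visit was expected, the Table 2 note says such women can be included, visits may be by telephone, and SAP 4.3 tabulates whether OGTT data were available when expected. The number of pregnancies and of OGTTs done at those visits is unknown.

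A third tempting reading is that the weight analysis also breaks a protocol rule. It does not: Protocol 3.6 attaches pregnancy censoring to the primary outcome only. For the continuous outcomes both documents are silent, and whether to include such measurements is partly a choice of estimand.

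Finally, comparing 76.9% with 88.8% would suggest a loss of about 12 points. That comparison treats censoring as free. Against the worst case for censoring at the two ends of the assumed range, the difference is 0.3 points (86.9% against 87.2%) to 6.5 points (76.9% against 83.4%).

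**Conclusion.** The concern holds as a failure to carry a stated protocol rule into the SAP's primary analysis, combined with a visit schedule that invites the measurements the rule was meant to keep out. That much follows from the text and is firm. The absence of any pregnancy rule for the continuous outcomes is a separate omission in both documents.

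The size is not known. Under the assumptions shown, a relative risk of 0.65 would read 0.67-0.73. The power cost relative to censoring ranges from negligible to about 6.5 points, and would be larger if censored women contribute earlier follow-up. Bias from unequal pregnancy rates is possible, but nothing in the documents indicates that rates differ. The case for change rests on having one unambiguous event and censoring definition that agrees with the protocol, more than on any particular power figure.

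**What to change.** Before unblinding:

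1. In SAP 4.9.2, 4.9.3 and 4.9.6, and for development of T2DM in 4.10, state that women with a subsequent pregnancy are censored at their last glycaemic assessment before the pregnancy, and that results obtained in pregnancy do not define events. Date the pregnancy by estimated conception if that is collected. Otherwise exclude the pregnancy-termination EOS visit and any visit at or after the date on which pregnancy was recorded.
2. In SAP 4.10.2 and 4.11.1, exclude weight, waist, hip, blood pressure, heart rate, FBG and HbA1c measured in pregnancy.
3. Report pregnancies by arm, and keep the analysis of all data as a sensitivity analysis.

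Protocol 3.6, Protocol 5.1.5 and SAP 3.5 must also be reconciled. Whether an OGTT is done at an EOS visit in pregnancy is a clinical matter and is not addressed here.

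The cost is SAP wording and some programming. Some EOS records leave the main models; at the assumed 5-15% this would concern about 71 to 212 of 1414 women. The protocol gives no censoring date, so the date in item 1 is a specification of its rule rather than a restatement. The documents do not show that a conception date is collected; the fallback would miss visits made after conception but before pregnancy was recorded.

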### 3.6 Calculation of durations

All durations (e.g. time to event) will be calculated relative to the date of randomisation, if not specified otherwise.

Age will be calculated from the Date of birth to date of randomisation. For analyses of age involving patients who were not randomised, age will be calculated using the date of informed consent instead of the randomisation date.

### 3.7 Definition of physical activity outcome

Physical activity will be measured in terms of Metabolic Equivalent for Task (MET) derived from the Global Physical Activity Questionnaire (GPAQ).

The total number of METs in a typical week will be used as secondary outcome. Other measures of physical activity, not considered as secondary outcomes, include:

- Hours of moderate physical activity (total hours per week)
- Sedentary hours (time spend sitting or reclining) (average hours per day)
- Hours of sleep (average hours per night)

### 3.8 Definition of diet outcome

Diet will be measured as the total calorie intake derived from the INTAKE 24 questionnaire. It is calculated as follows:

- Calories from carbohydrate = 4 x grams of carbohydrate
- Calories from protein = 4 x grams of protein
- Calories from fat = 9 x grams of fat
- Total calorie intake = calories from carbohydrate + calories from protein + calories from fat

The calculated total calorie intake will be used as secondary outcome. Other measures of diet, not considered as secondary outcomes, will include:

- Protein intake (grams)
- Carbohydrate intake (grams)
- Fibre intake (grams)
- Fat intake (grams)
- Sodium intake (grams)

### 3.9 Coding of adverse events and concomitant medications

Serious Adverse Events (SAE) and Concomitant Medications (CM) will be categorised by medical experts who will provide corresponding standard terms for free texts used for both SAE and CM. Coding will be performed while blinded to the treatment allocation.

### 3.10 Handling of Missing data

The number of patients with available data will be reported. Missing or incomplete data will not be substituted/imputed, except where explicitly stated throughout the SAP.

### 3.11 Presentation

Listings will be sorted by unique subject identifier and analysis time point and/or date if applicable. Dates will be formatted as DDMMYYYY. Partial dates will be presented on data listings as recorded on CRFs. Rounding for all variables will occur only as the last step, immediately prior to presentation in listings and tables.

No intermediate rounding will be performed on derived variables. The standard rounding practice of rounding numbers ending in 0-4 down and numbers ending 5-9 up will be employed. Every table, listing and figure will be produced with an electronic date stamp to document when it was produced.

### **3.12 Quality assurance**

Double programming by 2 independent Statisticians/Statistical programmers will be done on all key analyses. Double programming may be replaced by code review if need arises. Discrepancies and/or data handling decisions will be adjudicated by a third statistician without access to the impacted results.

## 4 Analysis details

---

### 4.1 General Principles

Analyses will be performed using SAS Enterprise Guide version 8.3 or higher (SAS Institute Inc., Cary, NC, USA).

All variables will be analysed by descriptive statistical methods. The number of data available and missing data, mean, standard deviation, minimum, quartiles, median, and maximum will be calculated for continuous data. Frequency tables will be generated for categorical data. For categorical variables, the number and percentage of patients with a specific level of the variable will be presented.

All tests will be two-sided with a type-I error rate of 5%. Analyses of the primary outcome (change in category of glycaemia from normoglycaemia to IGT, IFG or T2DM or from IFG or IGT to T2DM) will be unadjusted for multiplicity; however, we will control the family-wise error rate across secondary outcomes using a Holm-Bonferroni correction [2]. No other multiplicity adjustment will be applied.

### 4.2 Interim analyses

No interim analysis was conducted.

### 4.3 Subject disposition

The flow of subjects through the trial will be described using a Consort diagram (see Figure 1).

Screening failures will be listed together with the reason for their exclusion from study and all available data (Date of informed consent, Reason for screen failure, Date of last visit).

At each visit, we will tabulate the number and proportions of patients according to the following categories:

- Whether the visit took place (yes vs no)
- Reason for no assessment (e.g. early discontinuation, LTFU) – see Section 3.5
- Visit type (in hospital, at home, by telephone)
- Oral glucose tolerance test (OGTT) data available when expected (yes or no)
- Haemoglobin A1c (HbA1c) data available when expected (yes or no)
- Fasting blood glucose (FBG) data available when expected (yes or no)

### 4.4 Baseline characteristics

The following variables will be summarized at baseline:

- Socio-demographic characteristics
  - Age
  - Primary language
  - Country
  - Religion
  - Highest educational qualification (3 categories will be created: up to primary including none, secondary and other higher degree (diploma/undergraduate and graduate)
  - Years of schooling

- Current employment status
  - Current employment classification
  - Average household size of participant
- Risk Factors:
  - Reproductive history (Gravida, livebirths, time since delivery)
  - Family history
  - Obstetric history
  - Medical history (including history of hypertension and usage of hypertension medication)
  - Time since detection of GDM
  - Alcohol consumption
  - Tobacco consumption
- Vital Signs and anthropometric measures at baseline:
  - Height
  - Weight
  - Waist circumference
  - Waist circumference > 80 cm will be used to create a categorical variable separately
  - Hip circumference
  - Waist/Hip ratio
  - BMI
  - Blood pressure
  - Hypertension at baseline defined by SPB $\geq$ 140 and DBP $\geq$ 90
  - Heart rate
- Other Factors:
  - Use of insulin and pharmacotherapy during index pregnancy
  - Diet
  - Metabolic equivalent of task (MET) information at baseline(minutes/week)

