### 3.2 ELIGIBILITY CRITERIA

At each participating hospital, women with GDM will be identified at 24-34 weeks of gestation through the performance of a standard oral glucose tolerance test (OGTT) using the International Association of the Diabetes and Pregnancy Study Groups (IADPSG) criteria. If a patient has undergone assessment of glycaemic status prior to 24 weeks' gestation, an OGTT must be performed to confirm the diagnosis between 24 and 34 weeks' gestation, *unless* she is treated with an oral hypoglycaemic drug and/or insulin before 24 weeks, and satisfies the IADPSG criteria for diagnosis of GDM. If only FPG was done at 24-34 weeks, then she will be categorized as GDM/overt diabetes/ normal on the basis of FPG value alone (see Figure 2).

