**Scenario 2: OGTT at <24 weeks of gestation (scenario of second preference)**

[figure not shown]

**Scenario 3: FPG at <24 weeks of gestation (least favoured scenario)**[figure not shown]

These individuals will receive standard GDM care, but will also be exposed to an additional brief standardised educational program to improve knowledge of nutrition and physical activity both during and after pregnancy. The study will also be discussed, as establishing rapport with the participants at this stage will be important to maximise participation in post-pregnancy screening. Further contact will be made with potential participants on at least one occasion after hospital discharge, and prior to 3 months post-childbirth, when women will be invited for an OGTT to determine trial eligibility. Those diagnosed with T2DM using ADA criteria at this time will be referred for appropriate care; all other women will be eligible for trial participation.

The *inclusion* criterion, therefore, is the absence of T2DM (i.e. confirmation of NGT, IFG, or IGT) at 3 to 18 months post-partum OGTT. Consistent with design features of a pragmatic trial [29], *exclusion* criteria will be limited to:

- Confirmed case of Type 2 Diabetes

- Travel time to hospital more than 2 hours (unless individual circumstances will not impede hospital attendance for study visits)
- Lack of access to a mobile telephone
- Use of steroids during pregnancy other than for lung maturation of the baby
- Likelihood of moving residence in the next 3 years

All reasons for exclusion or consent refusal will be carefully recorded.

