**Table 3. Baseline characteristics**

| Characteristics                                                                                                                              | Intervention | Control | Total |
|----------------------------------------------------------------------------------------------------------------------------------------------|--------------|---------|-------|
| Age at randomization (years)
N
mean (SD)
Q1 Q2 Q3
Min, Max                                                                |              |         |       |
| Primary language
Tamil
Hindi
Telugu
Bengali
Sinhalese
Marathi
Konkani
..
..                                |              |         |       |
| Country
Bangladesh
India
Srilanka                                                                                            |              |         |       |
| Religion
Hindu
Muslim
Christian
Buddhist
Other                                                                         |              |         |       |
| Highest Educational Qualification
Primary (up to Primary including none)
Secondary
Other Higher degrees(Diploma/UG/Graduate) |              |         |       |
| Number of Years of Schooling
N
mean (SD)
Q1 Q2 Q3
Min, Max                                                                |              |         |       |
| Current Employment Status
Employed
Unemployed                                                                                   |              |         |       |
| Current employment classification

xx                                                                                           |              |         |       |

|                                                                          |  |  |  |
|--------------------------------------------------------------------------|--|--|--|
| Average Household Size
N
mean (SD)
Q1 Q2 Q3
Min, Max  |  |  |  |
| POG at diagnosis of GDM
N
mean (SD)
Q1 Q2 Q3
Min, Max |  |  |  |
| Early GDM (<=24 weeks)
Yes
No                            |  |  |  |
| Gravida>1
Yes
No                                         |  |  |  |
| Livebirth>=1
Yes
No                                      |  |  |  |

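### Two descriptive baseline rules in the SAP give wrong counts if programmed as written: hypertension requires both pressures raised, and early GDM includes week 24

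*Combined protocol and SAP*

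**What the plan says.** **Hypertension.** SAP section 4.4 lists among the baseline items "Hypertension at baseline defined by SPB $\geq$ 140 and DBP $\geq$ 90" (SPB is evidently SBP). The same section lists "Medical history (including history of hypertension and usage of hypertension medication" as a separate item. The Table 3 shell then has yes/no rows for systolic pressure of at least 140 and for diastolic pressure of at least 90, a row for antihypertensive medication, and two further yes/no rows headed *Hypertension* and *HTN%*. Neither of those two is defined, and nothing links either of them to the rule in 4.4.

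**Early GDM.** SAP Table 3 has a yes/no row "Early GDM (<=24 weeks", so week 24 counts as early. Protocol 3.2 says that "women with GDM will be identified at 24-34 weeks of gestation" and deals separately with the woman tested sooner: "If a patient has undergone assessment of glycaemic status prior to 24 weeks' gestation". Figure 2 of the protocol titles its second scenario "OGTT at <24 weeks of gestation (scenario of second preference", and the third scenario uses the same strict limit. The SAP's own inclusion criteria (2.3.1) draw the same line, with 24-34 weeks as the standard window and earlier tests handled by other criteria.

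**The concern.** Table 3 tells readers who was enrolled. Each of these rows is a stated rule, not a missing detail, so a programmer who follows the text will print the wrong number without noticing. The double programming in SAP 3.12 offers no protection, because two programmers working from the same sentence will agree with each other.

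For hypertension, the printed figure would leave out every woman with isolated systolic or isolated diastolic elevation. For early GDM, a woman diagnosed at 24 weeks under the protocol's preferred scenario would be reported as an early case, which conflicts with the protocol and with the SAP's own eligibility section. What is at stake is the accuracy of the baseline description only.

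**Working it through.** The plan states no figure that depends on either rule, so there is nothing to reproduce. The check is one of logic, plus an illustration of size.

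**1. Hypertension: logic.** Four example readings under the two rules:

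| Reading (mmHg) | Both raised (as written) | Either raised |
|---|---|---|
| 160/85 | no | yes |
| 135/95 | no | yes |
| 140/90 | yes | yes |
| 120/80 | no | no |

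Let S be the number with systolic pressure of at least 140, D the number with diastolic pressure of at least 90, and B the number with both. Then B cannot exceed S or D, and the either-raised number is E = S + D - B. Table 3 has rows for S and D, and possibly for B, but none for E.

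**2. Hypertension: size.** The documents give no blood pressure means, SDs or correlation. The values below are assumptions, with systolic and diastolic pressure taken as bivariate normal and cut-points at 140 and 90.

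| Assumed SBP mean (SD) | Assumed DBP mean (SD) | Correlation | Both | Either | Either ÷ both |
|---|---|---|---|---|---|
| 110 (12) | 72 (9) | 0.6 | 0.22% | 2.68% | 12.2 |
| 110 (12) | 72 (9) | 0.8 | 0.41% | 2.49% | 6.1 |
| 115 (13) | 76 (10) | 0.6 | 1.34% | 9.46% | 7.1 |
| 115 (13) | 76 (10) | 0.8 | 2.04% | 8.76% | 4.3 |
| 120 (15) | 80 (10) | 0.6 | 4.88% | 20.10% | 4.1 |
| 120 (15) | 80 (10) | 0.8 | 6.73% | 18.26% | 2.7 |

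Check of the first row: S = P(Z > (140 - 110)/12 = 2.5) = 0.62%, and D = P(Z > (90 - 72)/9 = 2.0) = 2.28%. So E = 0.62 + 2.28 - 0.22 = 2.68%.

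Across these inputs the rule as written misses between 1 - 6.73/18.26 = 63% and 1 - 0.22/2.68 = 92% of the women with either pressure raised. In the planned 1414 women that is 95 counted instead of 258 at one end, and 3 instead of 38 at the other.

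**3. Early GDM: side by side.**

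| Source | Early | Standard window |
|---|---|---|
| SAP Table 3 | 24 weeks or less | (remainder) |
| Protocol 3.2 text | before 24 weeks | 24-34 weeks |
| Protocol Figure 2, Scenarios 2 and 3 | under 24 weeks | 24-34 weeks (Scenario 1) |
| SAP 2.3.1 | before 24 weeks | 24-34 weeks |

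A diagnosis at 24 weeks satisfies both the Table 3 label and the standard window. How wide the overlap is depends on how gestation is recorded, which the documents do not say:

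- Weeks and days: only 24+0 overlaps, which is one day.
- Completed weeks: 24+0 to 24+6 overlap, which is seven days.

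If standard-window diagnoses were spread evenly (an assumption) over 24+0 to 34+6, which is 77 days, the overlap would hold 1/77 = 1.3% of them in the first case and 7/77 = 9.1% (1 in 11) in the second.

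**The case against.** The strongest reply is that nothing inferential uses either item. That is correct. Neither is a stratification factor (SAP 2.5), a term in the Cox or Poisson models (4.9.2, 4.9.3), an adjustment covariate (4.9.4), a subgroup (4.9.5) or a term in the mixed models (4.10.2). A reader might infer that the hypertension rule touches the systolic blood pressure outcome, but that outcome is analysed in mmHg with its own baseline value as covariate, and the flag never enters.

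Second, Table 3 already shows most of the blood pressure information: mean, SD and quartiles for each pressure, the two threshold rows, and medication. This stands in part. Each raised component is visible, and the either-raised number follows by addition and subtraction, but only if the reader knows which row holds the both-raised count and the rows share a denominator. The table does not say which row that is.

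Third, the documents contain no other definition of hypertension, and the sentence could be a loose way of naming two thresholds. This also stands: calling it wrong depends on the usual convention that either raised pressure suffices. As a programming instruction, though, the sentence has one literal reading.

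Fourth, the protocol never defines early GDM as a term; it only sets test-timing pathways, and the row sits in a table shell that also reports gestation at diagnosis as a continuous variable. The boundary is nevertheless drawn consistently everywhere else, including in the SAP's own eligibility section, so the label is the outlier.

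Two stronger readings are tempting and not supported. One is that week-24 diagnoses inflate early GDM by about 1 in 11 of the standard-window women; that needs completed weeks and an even spread, neither of which the documents state. The other is that the row marks diabetes present before pregnancy; the documents discuss pre-existing diabetes but do not tie it to early diagnosis.

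**Conclusion.** Both rules are wrong as written, and both are minor. The direction of the hypertension undercount is certain, since the both-raised count can never exceed the either-raised count. Its size is not: roughly 3- to 12-fold under the assumed pressures, and no narrower multiple can be defended from the documents. Treating the conjunction as an error rests on the either-pressure convention.

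The early-GDM label needs no outside convention. It contradicts the protocol and SAP 2.3.1, by one day or one week of gestation depending on how gestational age is recorded. The effect is confined to the baseline table.

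**What to change.** - SAP 4.4: replace *and* with *or* in the hypertension definition.
- SAP Table 3: state which of the *Hypertension* and *HTN%* rows carries this rule and define the other. If antihypertensive use or history is meant to count in either row, say so there.
- SAP Table 3: change the early-GDM label to under 24 weeks, matching protocol 3.2 and SAP 2.3.1.

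The cost is a few words in a short SAP amendment or documented clarification. The data are already collected, and no treatment comparison changes.
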